### Intervention

2.7

Electroacupuncture will be performed by the same licensed acupuncturist with 5 years of clinical experience in acupuncture. Prior to the trial, the acupuncturist will receive specific training on the treatment process (including the angle and depth of the needles, needle retention time, and needle insertion, travelling, and exit techniques) and will follow a standardized acupuncture protocol. A supervisory team will also be set up to monitor the acupuncturist’s acupuncture practice on site, and if any non-compliance with the protocol is detected, the acupuncturist will be corrected in a timely manner and the situation will be recorded.

#### Insomnia group

2.7.1

##### Sleep hygiene preaching

2.7.1.1

Patients will be instructed to pay attention to pertinent precautions at the time of enrollment, including good sleeping environments, such as indoor temperature, light, and humidity; regular work and rest; avoiding the consumption of excitatory food that affects sleep; and refraining from engaging in strenuous exercise before going to bed. The insomnia group received a unified sleep hygiene promotion.

##### Electro-acupuncture intervention

2.7.1.2

Insomnia patients will be treated with electro-acupuncture every other day, three times a week for four weeks, for a total of 12 times. Treatment will be carried out at Baihui, Yintang, Shenmen (double), and Sanyinjiao (double), and the positioning will be in strict accordance with the National Standard of the People’s Republic of China: Meridian Point Sites (GB12346-90) (**Figure 3**). Subjects will be placed in the prone position, and disposable sterile acupuncture needles (0.30 × 40 mm, Suzhou Medical Supplies Factory Co., Ltd.) will be used for needle insertion after routine sterilization. For the Baihui acupoint, the needle will be inserted at a 15° angle to the skin, to a depth of 0.5 - 0.8 inches. For the Yintang acupoint, the needle will be inserted at approximately a 15° or smaller angle, using a transverse technique, to a depth of 0.3 - 0.5 inches. For the Shenmen acupoint, the needle will be inserted perpendicularly (90°) to the skin, to a depth of 0.3 - 0.5 inches. For the Sanyinjiao acupoint, the needle will be inserted perpendicularly (90°) to the skin, to a depth of 1 - 1.5 inches. The acupuncture needle was inserted into the acupuncture point and lifted and twisted to achieve the state of getting qi. The low-frequency pulse electroacupuncture therapeutic instrument (Model XS-998B04 Low-Frequency Pulse Electroacupuncture Therapeutic Instrument, Nanjing Komatsu Medical Instrument Research Institute, Nanjing, China) will be connected to the needle handles of the Baihui and Yindang acupoints with a continuous wave pattern, a fixed frequency of 2Hz, and the stimulation intensity will be as tolerated by the subjects, and the needles will be activated after 30min of continuous stimulation.

**Figure 3 f3:**
[figure not shown]
The accurate positioning of acupuncture points.

#### Healthy group

2.7.2

The healthy group will not receive any treatment.

### Outcome assessment

2.8

#### Primary outcome

2.8.1

##### PSQI

2.8.1.1

A questionnaire was used to evaluate the quality of sleep in a population, including 7 components: sleep quality, time to sleep, sleep duration, sleep efficiency, sleep disorders, hypnotic medications, and daytime dysfunction. The total score of the PSQI is 0-21, and the level of the score is inversely related to the quality of sleep, i.e., the higher PSQI score suggests a worse quality of sleep. A score of ≥5 on the PSQI indicates that clinical treatment may be needed, and the present study used a PSQI score of 5 < PSQI < 17 points as the inclusion criteria for insomnia.

##### Metabolomics

2.8.1.2

Serum will be collected from the insomnia and healthy groups. Biomarkers associated with electroacupuncture treatment in insomnia patients will be identified through analysis and testing. In addition, the KEGG database will be used to analyze the metabolic pathways associated with these biomarkers, which will be used to explore the metabolic pathways involved in electroacupuncture for insomnia.

#### Secondary outcome

2.8.2

##### ISI

2.8.2.1

The purpose of the ISI is to assess an individual’s subjective perception of insomnia on a seven-question, five-point scale that participants fill out based on their sleep over the last week, with higher scores indicating more severe insomnia and greater distress to the individual. Scores range from 0-28. A total score of 0-7 indicates no insomnia distress, 8-14 indicates insomnia distress within the critical range, 15-21 indicates moderate insomnia distress, and 22-28 indicates severe insomnia distress.

##### HAS

2.8.2.2

HAS is used to evaluate the degree of trait arousal in the waking state of the patient, there are 26 items, and each item is scored 0-3 points, the total score is 0-78 points, the higher the score the higher level of cortical arousal of the patient. HAS > 32 points is considered to be the existence of an excessive arousal state.

##### FSS

2.8.2.3

The FSS is used to assess the level of fatigue. It consists of 9 entries evaluated at 7 score points, with a gradual transition from a score of 1 to 7 as strongly disagree to strongly agree. A total score below 36 indicates that fatigue may not be present, and a total score above 36 indicates that further evaluation may be required.

##### HAMA

2.8.2.4

HAMA is used to assess the severity of the patient’s anxiety symptoms and consists of 14 entries with a score of 0-4 for each item and a total score of 0-56, with higher scores representing more severe anxiety in the patient. HAMA score >14 is anxious and excluded.

##### HAMD

2.8.2.5

HAMD is used to assess the severity of the patient’s depressive symptoms and consists of 17 entries with a score of 0-4 for each item and a total score of 0-68, with higher scores representing a more severe level of depression. HAMA >17 is depressive and is excluded.

##### Sleep diary

2.8.2.6

Sleep diary, a standard subjective assessment tool for insomnia, is used to observe the severity of insomnia in patients and monitor sleep improvement during treatment, as well as a form of behavioral therapy. It records sleep information such as the previous night’s time of falling asleep, sleep latency, time of waking up in the morning, time of waking up, number and duration of waking up after falling asleep, total sleep time, time of falling asleep, and use of sedative-hypnotic drugs.

##### MoCA

2.8.2.7

The Montreal Cognitive Assessment (MoCA) is a 30-point scale that takes about 10 min to complete and assesses various dimensions of cognitive functioning: short-term memory, visuospatial executive ability, executive functioning, attention and working memory, language, and orientation in several dimensions of cognitive assessment. Years of education ≤12 scored an additional 1 point to correct for the effect of literacy. The higher the score, the better the cognitive function. A total score of ≥26 is considered normal.

#### Assessment time point

2.8.3

The insomnia group will have the above information completed at enrollment and after 12 treatments, the scale will be collected again at 3 months follow up, and the health group will have serum collected only at the first enrollment.

### Metabolomics

2.9

#### Sample collection

2.9.1

##### Requirements for blood sample collection

2.9.1.1

No caffeinated beverages or food (e.g., tea, chocolate, coffee, cola, etc.), no alcohol, and no food containing cheese and preservatives for 24h until sampling is completed;Avoid strenuous physical exercise for 24 hours before blood collection until sampling is completed;Avoid emotional stress on the day of blood collection and rest for at least 5 minutes before blood collection;Female subjects should avoid menstruation.

##### Collection and storage of blood samples

2.9.1.2

Venous blood was collected from the subjects, whole blood was collected in serum tubes, and the volume of blood collected was about 4mL, centrifuged at 4°C, 3500r/min for 10min. The upper layer of clear serum was extracted with a pipette gun to 400μL into 1.5ml graduated EP tubes with pointed bottoms, and then placed in a refrigerator at -80°C for storage and preparation for examination.

#### Metabolomics analysis

2.9.2

##### Metabolite extraction

2.9.2.1

Metabolite extraction was performed by the organic reagent protein precipitation method. Extraction method: take the cryopreserved serum samples, sorted according to the order of uptake, static thawing until completely liquid; take 40 μL of each sample and add it to the corresponding 96-well plate, add 120 μL of pre-cooled methanol, seal the membrane, shake and mix for 1 min, and place it in the refrigerator at -20 °C overnight; take it out on the next day, reconstitute the dissolution, and centrifuge it for 30 min under the condition of 4 °C, 4000 rpm, and then take 25 μL of the supernatant into a new 96-well plate, add 225 μL of 50% methanol for dilution, and then take it out on the following day. Take 25 μL of supernatant in a new 96-well plate, add 225 μL of 50% methanol for dilution, each take 60 μL of supernatant transferred to a new 96-well microtiter plate, according to the order of the uploading sequence, sealing the membrane marking, and ready for inspection. Take 20μL from each prepared sample and mix it into a prepared quality control sample (hereinafter referred to as “QC sample”).

#### Chromatography and mass spectrometry conditions

2.9.3

##### UPLC-Q-TOF-MS analysis

2.9.3.1

###### Chromatographic conditions

2.9.3.1.1

ACE Excel3 C18column (2.1 mm x 100 mm, 1.8 μm) was used; mobile phase: 0.1% formic acid in water (A)-0.1% formic acid in acetonitrile (B), gradient elution (0~2.5 min, 85%→80%A; 2.5~7 min, 80%-75%A; 7~12 min, 75%→50%A; 12~19 min, 50%→50%A; 12~19 min, 50%→50%A; 12~19 min, 50%→20%A; 19~23 min, 20%→54%A; 23~26 min, 54%→85%A; 26~35 min, 85%→85%A); Flow rate: 0.3 mL-min-1; Column temperature: 40 °C; Inlet volume: 5 μL; Inlet chamber temperature: 4°C.

###### Mass spectrometry conditions

2.9.3.1.2

the electrospray ionization (ESI) source was used to collect data in positive and negative ion modes; the parameters of the TOF-MS scanning mode were set as follows: relative molecular mass (RMM) scanning range of m/z50~1,000; accumulation time of 0.1500 s; ionization temperature (TEM) of 550 °C; nebulization gas (GS1) of 55 psi; auxiliary heated gas (GS2) of 55 psi; curtain gas (CUR) of 30 psi; de-clustering voltage (DP) 80 V; collision energy (CE) 5 eV; spray voltage (ISVF) in positive and negative ion modes were 5500, 4500 V. Data-dependent scanning (IDA), intelligent dynamic background subtraction (DBS), and high-sensitivity mass spectrometry data acquisition modes were used. The relative molecular mass (RMM) scanning range of the ion scanning mode was m/z50~1,000; the collision energy was (30 ± 15) ev, and the other main parameters were the same as those of the TOF-MS mode.

##### UPLC-QQQ-MS/MS analysis

2.9.3.2

###### Chromatographic conditions

2.9.3.2.1

ACE 5 C18-AR (4.6 mmx250 mm, 5 um); mobile phase: acetonitrile (A)-0.1% aqueous phosphoric acid (B), gradient elution (0~10 min, 2%→5%A; 10~20 min, 5%→20%A; 20~35 min, 20%→28%A; 35~40 min, 28%→30%A; 40 ~48 min, 30%→38%A; 48~50 min, 38%→2%A); detection wavelength: 280 nm; Flow rate: 1.0 mL-min-1; Column temperature: 40 °C; Injection volume: 20 μL.

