In order to investigate the pathophysiology of diseases and the mechanisms by which therapies work, metabolic technologies is used to identify the various changes that occur in biological systems under various medical conditions. It also facilitates the rapid and thorough analysis of differential metabolites to elucidate physiological or pathological pathways of metabolism (15). Additionally, the technology explores the relationship between pathophysiological changes and small molecule metabolites. 328 metabolites are thought to be very important in human sleep, and particularly abundant metabolites include carnitine, aromatic amino acids, phosphatidylcholine, and lysophosphatidylcholine (16).Previous studies have explored the unique serum metabolomic profile of insomnia and found that insomnia induces perturbations in metabolites of amino acid metabolism, neurotransmitter metabolism, and glycolipid metabolic pathways (17). One study showed that by collecting plasma from insomnia patients and applying untargeted metabolomics analysis, 64 metabolites were associated with sleep duration, and elevated levels of amino acid metabolites (such as branched-chain amino acids and gamma-glutamyl dipeptide) were associated with later sleep duration (18). In another study, elevated energy metabolites and reduced branched-chain amino acid catabolic metabolites, as well as altered glucose metabolism, were observed in patients with insomnia by comparing insomnia patients with healthy controls, suggesting an increased susceptibility to diabetes in insomnia patients (19). Insomnia leads to significant alterations in specific metabolic pathways, which may be evidence of a link between insomnia and other somatic and psychiatric disorders. Therefore, this study aims to utilize metabolomics techniques to qualitatively and quantitatively analyze the sera of healthy individuals and patients with insomnia, in order to screen for differential metabolites, further explore the possible pathogenesis of insomnia, and search for objective biomarkers for it.

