In addition, the development and translational application of metabolomics technology can not only be used to explore the pathogenesis of insomnia but also provide a new platform for constructing therapeutic strategies for insomnia. Studies have found that insomnia patients who take benzodiazepine receptor agonists and benzodiazepines have poor glucose metabolism (20), while exogenous melatonin significantly reduces glucose tolerance and increases insulin resistance in subjects (21). This suggests that medication may have adverse metabolic effects. A preliminary study of electroacupuncture Shenmen-Sanyinjiao acupoint pairing using non-targeted metabolomics techniques found that the Shenmen-Sanyinjiao pairing significantly potentiated serum glycerophosphatidylserine-like metabolites in patients with insomnia, resulting in a significant improvement in the impairment of diurnal functioning in insomnia patients (22). However, the current study lacked quantitative analysis of specific metabolites to observe the dynamic change pattern under electroacupuncture intervention. Therefore, it is necessary to conduct more in-depth studies to provide a scientific basis for the mechanism of action of electroacupuncture.

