###### Mass spectrometry conditions

2.9.3.2.2

electrospray ionization (ESI) source, negative ionization (ESI) mode; ion source temperature 350°C; spray voltage -3500 V; multiple reaction monitoring (MRM) mode: in collision gas mode; air curtain gas pressure 0.17 MPa; spray gas, pressure 0.34 MPa; auxiliary heating gas pressure 0.38 MPa.

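### The targeted UPLC-QQQ-MS/MS conditions do not match the Q/TOF screen they must validate, so candidates found only in positive mode or only at high organic content have no stated working assay in Group B

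*Protocol article*

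**What the plan says.** Serum metabolomics is one of the two primary outcomes (Protocol article, Abstract and section 2.8.1.2). Section 2.1 sets out two stages. Group A and the healthy group are screened by untargeted UPLC-Q/TOF-MS, and the selected metabolites are then quantified in Group B by targeted UPLC-QQQ-MS/MS. The Discussion presents the second stage as validation of the first.

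For the screen, section 2.9.3.1.1 gives 0.1% formic acid in water and in acetonitrile on a C18 column. Section 2.9.3.1.2 states that "the electrospray ionization (ESI) source was used to collect data in positive and negative ion modes".

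For the targeted stage, section 2.9.3.2.1 gives "ACE 5 C18-AR (4.6 mmx250 mm, 5 um); mobile phase: acetonitrile (A)-0.1% aqueous phosphoric acid (B), gradient elution". The last steps of the gradient are "30%→38%A; 48~50 min, 38%→2%A", and the section adds "detection wavelength: 280 nm; Flow rate: 1.0 mL-min-1". Section 2.9.3.2.2 gives "electrospray ionization (ESI) source, negative ionization (ESI) mode; ion source temperature 350°C; spray voltage -3500 V", read out by multiple reaction monitoring (MRM).

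On what may be found, the Introduction says of sleep-related compounds that "particularly abundant metabolites include carnitine, aromatic amino acids, phosphatidylcholine, and lysophosphatidylcholine". It also reports a preliminary electroacupuncture study in which treatment "significantly potentiated serum glycerophosphatidylserine-like metabolites in patients with insomnia".

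**The concern.** A validation assay has to be able to measure whatever the screen can select. Here it covers one polarity where the screen covers two, and a narrower range of solvent strength. Its eluent and its optical wavelength also belong to a different type of detector from the one named.

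What is at stake is the reading of a primary outcome. If a candidate from Group A cannot be measured in Group B for analytical reasons, its absence could be taken as a failure to replicate. The confirmed list would then partly reflect which compounds suit the assay rather than which differ in insomnia or respond to treatment. No second targeted method is described that would catch these candidates.

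**Working it through.** The plan gives no figure to reproduce, so the check sets the two stated methods side by side. In the screen, solvent A is water, so acetonitrile % = 100 − A%. In the targeted method, solvent A is acetonitrile, so acetonitrile % = A%.

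| Feature | Screen (2.9.3.1.1, 2.9.3.1.2) | Targeted (2.9.3.2.1, 2.9.3.2.2) |
|---|---|---|
| Acid | 0.1% formic | 0.1% phosphoric |
| Column | C18, 2.1 × 100 mm, 1.8 μm | C18-AR, 4.6 × 250 mm, 5 μm |
| Flow | 0.3 mL/min | 1.0 mL/min |
| Starting acetonitrile | 100 − 85 = 15% | 2% |
| Maximum acetonitrile | 100 − 20 = 80% (19 min) | 38% (48 min) |
| Polarity | positive and negative | negative only |
| Readout | mass spectrometry | MRM, plus a 280 nm wavelength |

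**Polarity.** The screen's positive-mode data have no counterpart in the targeted stage. A candidate seen only in positive mode has no stated assay. This follows from the text alone.

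**Organic range.** The ceilings differ by 80 − 38 = 42 percentage points. To place 38% on the screen's time axis, interpolate linearly:
- Rising: between 7 and 12 min acetonitrile goes from 25% to 50%, so 38% is reached at 7 + (38 − 25)/(50 − 25) × 5 = 9.6 min.
- Falling: between 23 and 26 min it goes from 46% to 15%, so 38% is passed at 23 + (46 − 38)/(46 − 15) × 3 ≈ 23.8 min.
- Time above 38%: 23.8 − 9.6 ≈ 14.2 of 35 min.

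This takes the 12 to 19 min step as 50% to 80% acetonitrile; the printed gradient repeats that interval with inconsistent values. The result shows that the screen spends substantial time beyond the targeted ceiling. It does not count metabolites.

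**Detector.** Three facts used here are general analytical chemistry and are not stated in the document: phosphoric acid is non-volatile and unsuited to electrospray; 280 nm is a UV setting with no role in MRM; and carnitines and choline-headgroup lipids are normally measured in positive mode. The polarity and gradient mismatches stand without the first two.

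**Which candidates are exposed.** Given that chemistry, carnitines are exposed through polarity. Phospholipids may be exposed through the gradient, if the screen elutes them above 38% acetonitrile. Acidic or polar compounds that ionise in negative mode and elute by 38% are not excluded on either ground.

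**The case against.** The strongest reply is that nothing has yet been shown to fail. The candidates are unknown until Group A is analysed. The Introduction also names amino acids, dipeptides and energy metabolites, for which no polarity or gradient barrier has been shown. An optical wavelength next to an MRM readout looks like HPLC-UV conditions copied into the wrong place, and the article has other slips. Section 2.11 says that operating and quality control procedures for this technique will be established. MRM is set up target by target, so a compound without a workable transition could be recognised as not assayed.

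Much of this stands, and it limits the point. A reader might infer more than the document supports in four ways:
- *That validation must fail for whole metabolite classes, such as three of the four named in the Introduction.* The document says nothing about how these compounds ionise or are retained. Nor does it show that the screen, which itself stops at 80% acetonitrile, elutes the phospholipids.
- *That about half of the candidates are lost.* On the rising part of the gradient, (19 − 9.6)/19 = 49% lies above 38%; over the whole run it is 14.2/35 ≈ 41%. Both are shares of time, depend on the denominator, and would need similar retention on two different columns with different acids, starting points and slopes.
- *That Group B contributes nothing else.* Its patients also supply the PSQI, the other primary outcome, and the secondary scales.
- *That the targeted column and flow rate must copy the screen's, or that the lack of a wash step is an error.* The first is a preference; the second is a detail that an article may leave out.

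The possibility of a copying error does not remove the point. The conditions are given in detail, they conflict with the stated purpose, and the document offers no other targeted method. If it is only an error of text, the text needs correcting.

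**Conclusion.** The concern holds as a mismatch between two stated methods. The targeted run covers one of the screen's two polarities and up to 38% of its 80% acetonitrile, and it names an acid and a wavelength that do not suit an ESI/MRM readout. Candidates detected only in positive mode, or eluting only at higher organic content, have no stated working assay in Group B. This may include carnitines and phospholipids. The number or share affected cannot be derived from the document.

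The polarity and organic-range mismatches rest on the text alone. That late-eluting candidates would be missed assumes broadly similar C18 retention. The unsuitability of the eluent and wavelength, and the likely exposure of particular classes, rest on general analytical chemistry. The scale outcomes are unaffected.

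**What to change.** Before any Group B serum is run, correct sections 2.9.3.2.1 and 2.9.3.2.2 so that the targeted method has:
- an MS-compatible volatile eluent, for example the 0.1% formic acid already used for the screen;
- a gradient that covers the screen's organic range;
- MRM in the polarity in which each candidate was detected;
- no 280 nm wavelength.

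Add a reporting rule: a candidate that the final method does not detect in the pooled QC sample (section 2.9.2.1) is reported as *not assayed*, not as *not validated*, and validation claims are limited to candidates it does detect.

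The cost is a methods amendment, a short method set-up and possibly a second injection per sample. Serum is stored at −80 °C (section 2.9.1.2), so no extra patients or visits are needed.

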###### Mass spectrometry conditions

2.9.3.2.2

electrospray ionization (ESI) source, negative ionization (ESI) mode; ion source temperature 350°C; spray voltage -3500 V; multiple reaction monitoring (MRM) mode: in collision gas mode; air curtain gas pressure 0.17 MPa; spray gas, pressure 0.34 MPa; auxiliary heating gas pressure 0.38 MPa.

###### Data preprocessing

2.9.3.2.3

The UPLC/Q-TOF-MS system operating software MassLynx (SCN633) was used to preprocess the raw data related to metabolomics. The program automatically carried out pre-processing tasks like noise filtering, mass spectral peak identification, and normalization. Ultimately, a three-dimensional data matrix that included retention time, mass-to-charge ratio, and spectral peak area was produced.

